# Comparing an optimised physiotherapy treatment package with usual physiotherapy care for people with tennis elbow — protocol for the OPTimisE pilot and feasibility randomised controlled trial

**DOI:** 10.1186/s40814-022-01132-x

**Published:** 2022-08-11

**Keywords:** Physiotherapy, Physical therapy, Lateral elbow tendinopathy, Tennis elbow, Pilot, Feasibility

## Abstract

**Background:**

Physiotherapy is recommended for people with tennis elbow, but whilst a wide array of treatments is available, the optimal approach remains uncertain. We have therefore recently developed an optimised physiotherapy treatment package for tennis elbow based on a synthesis of the evidence, patient input and clinical consensus. It consists of detailed advice and education, a structured progressive exercise programme and provision of a counter-force elbow brace. Here, we report the protocol for our multicentre pilot and feasibility randomised controlled trial (RCT) designed to (a) examine the feasibility of our optimised physiotherapy treatment package and (b) to pilot trial processes for a future fully powered RCT to test clinical and cost-effectiveness compared with usual physiotherapy treatment.

**Methods:**

A multicentre pilot and feasibility RCT will be conducted across three sites in England, recruiting up to 50 patients (or for a maximum of 12 months). Participants with tennis elbow, identified from physiotherapy clinic waiting lists and general practice surgeries, will be randomly allocated to receive the optimised physiotherapy treatment package or usual physiotherapy care. Analysis will focus on feasibility measures including consent rate, intervention fidelity, follow-up rate and outcome completion rate. A nested qualitative study will explore the acceptability of the study processes and patient and physiotherapist experiences of the new optimised intervention.

**Discussion:**

This study will determine the feasibility of a new optimised physiotherapy treatment package for people with tennis elbow and pilot the processes for a future fully powered RCT. In the longer term, this treatment package may provide superior clinical outcomes for patients, in terms of pain and quality of life, and be more cost-effective for the health service.

**Trial registration:**

Registered with the ISRCTN database 19/7/2021, https://www.isrctn.com/ISRCTN64444585

## Introduction

### Background and rationale

Tennis elbow, also known as lateral elbow tendinopathy, is a musculoskeletal condition that usually affects people in middle age and often affects an individual’s ability to work [1, 2]. In 2012, absenteeism from work due to tennis elbow cost the UK economy £27 M [3]. Common risk factors for onset have been identified as repetitive handling of heavy loads, forearm rotating motions, strong gripping force and working postures that combine force or load handling with raised arms [4]. Whilst the condition is self-limiting for many patients, 8.5–17% of individuals will have persistent symptoms, lasting more than 12 months [2, 5, 6]. Physiotherapy is recommended, but research has shown that physiotherapy treatment for tennis elbow varies widely and is suboptimal [7, 8]. In order to improve the physiotherapy treatment for people with tennis elbow, we recently developed an optimised physiotherapy treatment package by triangulating the best available research evidence, with consensus from UK physiotherapists with a special interest in tennis elbow, physiotherapy service managers and patient representatives, to ensure the intervention designed was acceptable to all stakeholders. A detailed description of this treatment package and how it was determined can be found in the open-access intervention development paper [9].

Improved physiotherapy provision for patients with tennis elbow has the potential to reduce pain, improve quality of life, reduce time off work and reduce the number of patients developing persistent symptoms. When physiotherapy fails to help, the usual pathway involves costly alternative treatments such as injections (of various types, e.g. autologous blood/platelet-rich plasma/corticosteroid/sodium hyaluronate) or surgery, but there is limited evidence for the effectiveness of these procedures [10, 11]. Surgery, however, is on the rise, for example in the USA there was a threefold increase between 2000 and 2011 [2]. In England, 2845 surgeries were performed in 2019/2020 at a cost of £1086 per procedure (total £3.1 million). If physiotherapy can be improved such that more patients with tennis elbow benefit, then fewer patients may subsequently require injections and surgery with associated cost-savings.

The newly designed optimised physiotherapy treatment package is therefore ready for feasibility and pilot trial testing, prior to conducting the main randomised controlled trial (RCT).

### Objectives

To report the protocol for a multicentre pilot and feasibility RCT, aimed at examining the feasibility of our optimised physiotherapy treatment package and piloting trial processes for a future fully powered RCT to test clinical and cost-effectiveness compared with usual physiotherapy treatment.

Specific objectives are as follows:Estimate participant recruitment, outcome measure completion and follow-up rates in a pilot RCT.Assess patient and clinician fidelity to the optimised intervention.Explore the acceptability of the optimised physiotherapy treatment programme from both the perspective of patients and physiotherapists.

## Methods

### Trial design

This is a mixed-methods pilot and feasibility RCT with nested qualitative study (see Fig. 1).

**Fig. 1 Fig1:**
[figure not shown]
Study flowchart

### Study setting

The study will be conducted at three National Health Service (NHS) sites in England providing outpatient musculoskeletal physiotherapy for adult patients with tennis elbow.

### Patient eligibility criteria and identification

Patients will be included in the pilot and feasibility trial if they are adults aged 18 or over, with physiotherapist determined tennis elbow, have pain on palpation of the common extensor origin and on gripping and have either a positive Cozen’s, Mills', or Maudsley’s test [12]. Exclusion criteria include the following: a recent history of significant trauma to the affected limb, e.g. a fall on an outstretched hand, previous diagnosis of inflammatory arthritis or gout and previous diagnosis of osteoarthritis of the affected elbow, and neurological symptoms in the affected limb correlating with onset of elbow pain, e.g. loss of sensation in the hand, co-existing neck pain and stiffness that started at a similar time to the elbow symptoms, inability to understand English or lacking capacity for informed consent or are currently enrolled in another health-related research trial.

Patients with tennis elbow will be identified using one of two methods:By screening patient referrals at the three NHS primary care outpatient physiotherapy providers. Prior to attendance in the physiotherapy clinic, all primary care referrals will be screened by a physiotherapist, as is normal practice, and those patients who are potentially eligible will be sent a patient information sheet (PIS). The physiotherapist will then telephone the patient (typically 1–2 weeks later) to discuss the trial and book an appointment for an eligibility assessment with a research physiotherapist, if interested.By screening the SNOMED CT NHS database for patients in those three catchment areas with a diagnostic coding of tennis elbow in primary care within the last 3 months. Potentially eligible patients will be identified from the SNOMED CT database by a member of staff at participating GP practices in the locality. They will be sent a PIS by post along with a screening questionnaire and letter of introduction by the practice administrator. If interested and meeting the screening criteria, they will be asked to contact the Clinical Trials Unit (CTU) via the OPTimisE trial website. The principal investigator (PI) at the local trial site and their GP will then be informed of their interest to participate, and the GP will be requested to refer the patient to physiotherapy.

### Recruitment

Patients identified in the initial screening process will attend for clinical assessment by a physiotherapist trained in the OPTimisE protocol, to establish the diagnosis of tennis elbow and do a final confirmation of eligibility based upon the inclusion/exclusion criteria. Travel expenses for this initial patient visit (for eligibility assessment) will be offered. Patients meeting the eligibility criteria will be invited to participate in the RCT and consent gained as per Good Clinical Practice guidelines including an explanation of the condition, reassurance about receiving treatment, establishment of uncertainty as to the optimum physiotherapy treatment approach, an explanation of the study purpose, a balanced view of the two interventions, rights to withdraw, and an explanation of study procedures. There will be opportunity to discuss and ask questions before providing written consent via the trial consent form. Patients who decline to take part in the pilot and feasibility trial will be invited to be interviewed as part of the qualitative feasibility component. Those willing to be interviewed will be required to provide written consent to be contacted in relation to the interviews.

### Sample size

The pilot and feasibility RCT will recruit up to 50 participants or for a maximum of 12 months across three sites. These limits were a condition stipulated by the funder. The nested qualitative study will recruit until data saturation, estimated as up to 25 participants (approximately 16 patients and 9 treating physiotherapists).

### Assignment of interventions

#### Allocation sequence generation

Patients will be randomised in a 1:1 allocation (in mixed blocks) stratified by site using an online randomisation service provided by the CTU. Mixed blocks are required to reduce the predictability of the randomisation allocations.

#### Implementation and allocation concealment

The site PI or person delegated to take consent and randomise patients will use the online randomisation service ‘Sealed Envelope’ to access the allocation. This is an independent system to ensure allocation concealment.

#### Blinding

Due to the nature of physiotherapy treatments, it is not possible to blind participants to their treatment allocation. The treating physiotherapists will be blinded to the outcome measure data until the final results of the trial are reported. Outcome measure data will be collected and analysed by the research team.

### Interventions

Patients will be randomly allocated to receive either the optimised physiotherapy treatment package, by physiotherapists specifically trained to deliver this, or usual physiotherapy care delivered by other physiotherapists not trained in the optimised intervention but trained in the RCT procedures.

#### Usual care

Usual NHS physiotherapy will not be standardised in this pragmatic study, but the details of the content and number of treatments given will be captured at the end of a patient’s course of physiotherapy. The site PI, or delegated person at site, will review each patient’s physiotherapy notes and complete a case report form (CRF). Usual physiotherapy may involve a range of different treatments including advice and education, exercise, taping, manual therapy, acupuncture, ice therapy, orthotics, and massage [7, 8]. Evidence suggests that there is inconsistency of approach and a wide range of variation within treatment categories, for example the dosing of exercise therapy [8, 13].

#### Optimised intervention

The optimised physiotherapy treatment package includes patient advice and education, exercise therapy, and provision of a counterforce brace. It will differ from usual care by providing a detailed and consistent approach to treatment based upon best available evidence and omitting treatments lacking evidence of efficacy, such as taping, acupuncture and therapeutic ultrasound. The advice and education component is detailed and supported by high-quality written and videographic materials, developed in consultation with patients. The topics covered not only relate to tennis elbow but also incorporate modifiable lifestyle factors that may improve treatment response and reduce risk of recurrence (Table 1).

**Table 1 Tab1:** The advice and education topics included in the optimised physiotherapy treatment package

Condition-specific advice	General/lifestyle factor advice
What tennis elbow is	Basic pain science
Activity modification	Promotion of self-efficacy
Pacing	General exercise advice
Ergonomics for work or sport	Smoking cessation (if applicable)
Medication advice	Sleep advice
	General diet advice
	Diabetes management (if applicable)

The exercise therapy component consists of a progressive regime incorporating stretching, isometric loading, concentric loading and eccentric loading designed to be adaptable to individual patient’s functional demands. Dosage is clearly defined based upon best evidence, and a novel aspect is that patients will be encouraged to exercise into levels of pain deemed acceptable by the individual patient. Painful exercise has been avoided in the interventions tested in the majority of tennis elbow trials to date, but recent systematic review evidence from the fields of back pain, shoulder pain and heel pain trials suggests it may offer improved short-term pain relief [14].

### Outcomes

The primary outcomes for this pilot and feasibility study are as follows (see Table 2):Consent rateIntervention fidelity in the intervention groupFollow-up rate in the intervention groupOutcome measure completion rate at 6 months

**Table 2 Tab2:**

Feasibility criteria for a future main trial

The secondary outcomes for the study are as follows:Adherence to exercise therapy treatmentOutcome measure completion rate at 6 weeks and 3 monthsPatient-reported outcomes (see Table 4)Completion of physical measures using the Squegg deviceResponsiveness analysis of outcome measuresAcceptability of the optimised physiotherapy treatment package and trial processes, determined by the nested qualitative study

### Participant timeline (Table 3)

### Data collection methods

Once consented and prior to randomisation, participants will complete a baseline set of patient-reported outcome measures (PROMs) and demographic data including age, gender, ethnicity, duration of symptoms, occupation, education level, hand dominance and comorbidities. Physical measures of maximum grip strength and pain-free grip strength will be taken by the PI or person delegated to take consent, using an electronic grip strength measuring device (Squegg, https://mysquegg.com/). The Squegg is a US Food and Drug Administration (FDA)-approved dynamometer. Both measures will be repeated three times and a mean value used for analysis.

Patients will be offered the choice of two data collection methods for subsequent follow-up: (1) a paper questionnaire with follow-up questionnaires delivered and returned by post to the CTU or (2) an online system provided by Amplitude Clinical where the questionnaires are completed online using a smartphone, tablet or personal computer with automated follow-up questionnaire links delivered by email and SMS text message.

Patient-reported outcome follow-up data collection will be at 6 weeks, 3 and 6 months using the OPTimisE Follow-up Questionnaire. Patients who do not return the paper questionnaires within 2 weeks will receive reminder telephone calls and emails (according to patient preference) on up to two occasions from the chief investigator. Those who do not respond to the online questionnaires will receive automated reminders by email and SMS text message at 1 week and 2 weeks. The choice of outcome measures includes the core outcome set recently recommended for tennis elbow [21]. See Table 4 below:

The physical measures of maximum grip strength and pain-free grip strength will also be reported by patients using the OPTimisE Follow-up Questionnaire. Patients randomised to the OPTimisE intervention will be given a Squegg device to take home at their initial research visit with an information sheet on how to use it. The OPTimisE Follow-up Questionnaire will prompt the patients to use the Squegg device and document three measures each of maximum grip strength and pain-free grip strength. Patients in the usual physiotherapy group will be sent a Squegg device at 6 months. As the device can be used for grip strength training and is not provided as part of usual physiotherapy care, it will only be used at the 6-month time-point for patients in the usual physiotherapy group, to avoid intervention contamination.

Fidelity of the optimised physiotherapy intervention will be measured retrospectively by reviewing the CRF data to establish whether the treatments provided matched the pre-defined protocol. Fidelity will be calculated as a percentage based upon the number of applicable treatment items delivered. Any additional interventions will be noted and discussed in the final data analysis and report. Similarly, CRF data will be used to review the treatment of patients receiving usual physiotherapy to assess for key differences and similarities between the interventions and determine whether there is contamination between the interventions. Adherence to treatment will be measured in both treatment arms using a patient-reported exercise diary that is reviewed by the treating physiotherapist at each session and returned to the chief investigator by the patient after 3 months, via a stamped addressed envelope. Additionally, the 6-week, 3- and 6-month outcome questionnaires will include the Exercise Adherence Rating Scale [20]. Participants will receive a £20 voucher after completing all of the study questionnaires at 6 months.

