### Data management

Data will be collected using a mix of paper and electronic methods. Where possible, a patient ID number will be used rather than identifiable information. Data from paper forms will be transcribed into an electronic database in Microsoft Excel stored on secure servers provided by the sponsor. Paper hard copies will be stored at the CTU and in the relevant Investigator Site Files. Study documentation will be stored securely (i.e. cupboards, shelves or filing cabinets with restricted access, e.g. within a locked office) to maintain participant confidentiality and study data integrity.

Electronic data captured at trial sites will be sent to the research team by secure NHS email. Online outcome data collection will be managed by Amplitude Clinical in ISO27001 Tier 3+ data centres approved for use by the NHS. Amplitude Clinical will not own the data — ownership is retained by the sponsor.

In order for patients to use the Squegg device, they will need to install the Squegg app on an Apple or Android smartphone/tablet. They are required to create an account within the app or log in using a Facebook or Google account. For data privacy reasons, participants will be recommended to use an email address rather than Facebook to create a user account; however, this is their own personal choice. No data will be shared between Squegg and the research team. Patients will use the device to measure grip strength and report the numerical values on the OPTimisE Follow-up Questionnaire.

Qualitative data will be organised and managed using NVivo software. Audio recordings and transcriptions will be stored on secure servers provided by the sponsor. An NHS-approved transcription service will be used that complies with data security regulations.

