**Table 3 Tab3:**
[figure not shown]
Schedule of events

*t*_0_ additional research clinic appointment *t*_1_ first physiotherapy treatment clinic appointment

Mean values and confidence intervals of the secondary outcomes (see Table 4) will be calculated if the data are normally distributed (this will be assessed using a combined test of skewness and kurtosis). If the data are not normally distributed, medians and interquartile ranges will be reported. The responsiveness of the different outcome measures will be compared, by calculating the treatment effect in the intervention group.

**Table 4 Tab4:** Outcome measures and time-points

Outcome measure	Baseline	6 weeks	3 months	6 months
Numerical rating scale of pain on gripping	X	X	X	X
Patient-rated tennis elbow evaluation (PRTEE) [15]	X	X	X	X
Tampa scale of kinesiophobia (TSK-11) [16]	X	X	X	X
Pain self-efficacy questionnaire (PSEQ) [17]	X	X	X	X
EQ 5D5L [18]	X	X	X	X
Pain-free grip strength (lbs)	OPTimisE group X	OPTimisE group X	OPTimisE group X	OPTimisE group X
	Usual care group X	Usual care group	Usual care group	Usual care group X
Maximum grip strength (lbs)	OPTimisE group X	OPTimisE group X	OPTimisE group X	OPTimisE group X
	Usual care group X	Usual care group	Usual care group	Usual care group X
Global perceived effect (GPE-11) [19]		X	X	X
Exercise adherence rating scale (EARS) [20]		X	X	X

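### Grip strength is staff-administered at baseline and self-administered at every follow-up, so a responsiveness estimate based on change from baseline would mix recovery with a change of measurement mode

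*Protocol article*

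**What the plan says.** All references are to the protocol article.

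- **Baseline.** The Data collection methods section says: "Physical measures of maximum grip strength and pain-free grip strength will be taken by the PI or person delegated to take consent". This happens after consent and before randomisation. The footnote to Table 3 describes t0 as an "additional research clinic appointment". Each measure is taken three times and the mean is analysed.
- **Follow-up, both arms.** The same section says: "The physical measures of maximum grip strength and pain-free grip strength will also be reported by patients using the OPTimisE Follow-up Questionnaire". The Data management section agrees: "Patients will use the device to measure grip strength and report the numerical values on the OPTimisE Follow-up Questionnaire". It adds that nothing passes from the device supplier to the research team.
- **Follow-up, OPTimisE arm.** These patients "will be given a Squegg device to take home at their initial research visit with an information sheet on how to use it", and the questionnaire "will prompt the patients to use the Squegg device and document three measures each of maximum grip strength and pain-free grip strength". Table 4 schedules this at 6 weeks, 3 months and 6 months.
- **Follow-up, usual care arm.** "Patients in the usual physiotherapy group will be sent a Squegg device at 6 months". Apart from baseline, this is the arm's only grip time-point.
- **Analysis.** Responsiveness of the outcome measures is a listed secondary outcome. The Statistical methods section says: "The responsiveness of the different outcome measures will be compared, by calculating the treatment effect in the intervention group". Table 4 includes both grip measures among the outcome measures.

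**The concern.** Responsiveness asks how strongly a measure registers change. To compare measures fairly, each should be obtained in the same way at both ends of the interval. For grip, the person administering the test changes exactly where baseline ends and follow-up begins. No reading links the two modes, so the analysis cannot separate a mode difference from recovery.

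Pain-free grip is the more exposed of the two, because the value depends on when the patient decides to stop, and a staff member running the test could plausibly influence that. The pain rating, PRTEE, TSK-11, PSEQ and EQ-5D-5L are completed by the patient throughout. A mode shift could therefore make grip look more or less responsive than these for reasons unrelated to the elbow.

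This is separate from the article's own worry that the device can serve as a training tool. The mode shift would arise even if nobody trained with it.

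**Working it through.** The article states no figure for a mode effect or for change in grip, so there is nothing to reproduce. The first check is of the text.

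**Step 1: who produces the value, by time-point**

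| | Baseline | 6 weeks | 3 months | 6 months |
|---|---|---|---|---|
| Grip, OPTimisE arm | staff | patient | patient | patient |
| Grip, usual care arm | staff | not scheduled | not scheduled | patient |
| Questionnaire measures with a baseline value | patient | patient | patient | patient |

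The device type and the three readings per measure are the same in both modes. What changes for grip is the operator, the supervision, the setting and the recording. Setting also changes for the questionnaires, from the research visit to post or online. The change of operator is specific to grip.

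**Step 2: which contrasts are affected**

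- Baseline to any follow-up, within an arm: the mode changes, so the contrast is affected.
- Follow-up to follow-up, within the OPTimisE arm: patient to patient, so the operator does not change.
- OPTimisE against usual care at 6 months: patient-taken in both arms, so a common shift largely cancels. The arms may differ in practice with the device, because OPTimisE patients have had it from the start.

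**Step 3: what the responsiveness analysis uses**

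The planned quantity is an effect within one arm. For a measure with a baseline value, the natural one-arm effect is change from baseline, which is the affected contrast.

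**Step 4: illustrative size**

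The SD of change and the shifts below are assumptions, and the direction is unknown.

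Standardised shift = shift / SD of change, with SD 20 to 25 lb:

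- 2 lb: 2/25 to 2/20 = 0.08 to 0.10
- 5 lb: 5/25 to 5/20 = 0.20 to 0.25
- 10 lb: 10/25 to 10/20 = 0.40 to 0.50

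For scale, take the standardised response mean (SRM), which is mean change divided by the SD of change. Up to 50 participants allocated 1:1 gives n = 50/2 = 25 in the intervention arm. SE(SRM) ≈ √(1/n + SRM²/(2n)):

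- SRM 0.5: √(0.04 + 0.25/50) = √0.045 = 0.21
- SRM 0.8: √(0.04 + 0.64/50) = √0.0528 = 0.23

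A 2 lb shift is well inside one standard error, a 5 lb shift is about one, and a 10 lb shift is about two. Unlike sampling error, the shift does not shrink with more patients.

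**The case against.** The strongest reply is that the whole consequence hangs on one ambiguous sentence in a condensed article. Several stronger readings are tempting, and the document does not support them.

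- **That change from baseline is specified.** It is not written; it is inferred from a one-arm effect. The other planned summaries are means with confidence intervals, or medians with interquartile ranges, not change scores.
- **That the comparison will choose the main trial's outcome measures.** The article does not say so. The estimates it ties to informing a main trial are the consent, fidelity, follow-up and completion rates.
- **That only grip is collected differently at follow-up.** Setting changes for the questionnaires too. Only the move from staff to self-administration is particular to grip.
- **That the shift would reorder the measures.** No responsiveness value is given for any measure and the pound figures are assumed, so reordering is not shown. With about 25 patients the ranking is imprecise anyway.
- **That grip must be dropped from the comparison.** It need not be, because same-mode contrasts exist between follow-ups.

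It is also fair to say that home self-measurement is part of what is being piloted, since completion of the Squegg measures is itself a secondary outcome. In addition, the instruction sheets are not shown, so how far the two procedures differ in practice is unknown.

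These points limit the severity and the claims about size. They do not remove the core: the article states a staff-taken baseline and patient-taken follow-ups and describes no bridging reading. A statistical analysis plan could not supply a self-taken baseline afterwards.

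**Conclusion.** The point holds as a minor design improvement. If responsiveness is judged on within-arm change from baseline, the grip estimates are confounded with a change from staff-administered to self-administered measurement, by an amount and in a direction that the design cannot estimate. The numerical illustration rests wholly on an assumed SD of change and assumed shifts; it shows scale and is not evidence that a shift exists. The between-arm comparison at 6 months, the Squegg completion outcome and the four progression criteria are essentially untouched. Grip is secondary and the analysis descriptive, so nothing in the trial's main conclusions depends on this.

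**What to change.** **If baseline collection can still be changed.** At the baseline visit, before randomisation, have participants take the three maximum and three pain-free readings themselves on the site's Squegg, following the same written instructions that are used at home. Staff only record the values, and these serve as baseline. This changes a visit instruction and needs no extra visit, device or staff. The cost is slightly noisier baseline readings. It aligns operator and instructions but not supervision or setting, because the reading is still observed in clinic, so it reduces the mode difference without removing it.

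**If staff have already taken the baseline readings.** Keep grip in the responsiveness analysis. Add the same-mode change from 6 weeks to 6 months in the OPTimisE arm, and report the questionnaire measures over that interval too so that the comparison is like with like. Flag the baseline-based grip responsiveness as confounded with the change of mode. This costs a few table rows and a sentence. Its limit is that it misses change in the first 6 weeks.

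In either case, state in the Statistical methods section which contrast the one-arm effect refers to.
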